# Efficacy and safety of deep brain stimulation in mesencephalic locomotor region for motor function in patients with post-stroke hemiplegia: a study protocol for a multi-center double-blind crossover randomized controlled trial

**DOI:** 10.3389/fneur.2024.1355104

**Published:** 2024-08-13

**Keywords:** deep brain stimulation, hemiplegia, motor dysfunction, motor recovery, stroke

## Abstract

**Background:**

Deep brain stimulation (DBS) is a potential treatment for improving movement disorder. However, few large-sample studies can reveal its efficacy and safety. This study aims to initially explore the efficacy and safety of DBS in the mesencephalic locomotor region (MLR) on motor function in patients with post-stroke hemiplegia.

**Methods/design:**

This multicenter, prospective, double-blind, randomized crossover clinical trial aims to assess the safety and effectiveness of Deep Brain Stimulation (DBS) in the mesencephalic locomotor region (MLR) for patients with moderate to severe post-stroke hemiplegia. Sixty-two patients with stable disease after a year of conservative treatment will be enrolled and implanted with deep brain electrodes. Post-surgery, patients will be randomly assigned to either the DBS group or the control group, with 31 patients in each. The DBS group will receive electrical stimulation 1 month later, while the control group will undergo sham stimulation. Stimulation will be discontinued after 3 and 6 months, followed by a 2-week washout period. Subsequently, the control group will receive electrical stimulation, while the DBS group will undergo sham stimulation. Both groups will resume electrical stimulation at the 9th and 12th-month follow-ups. Post-12-month follow-up, motor-related scores will be collected for analysis, with the Fugl-Meyer Assessment Upper Extremity Scale (FMA-UE) as the primary metric. Secondary outcomes include balance function, neuropsychiatric behavior, fall risk, daily living activities, and quality of life. This study aims to provide insights into the therapeutic benefits of DBS for post-stroke hemiplegia patients.

**Result/conclusion:**

We proposed this study for the first time to comprehensively explore the effectiveness and safety of DBS in improving motor function for post-stroke hemiplegia, and provide evidence for DBS in the treatment of post-stroke hemiplegia. Study limitations are related to the small sample size and short study period.

**Clinical Trial Registration:**

Clinicaltrials.gov, identifier NCT05968248.

## Introduction

The number of stroke patients worldwide has exceeded 20 million, making it the third largest disease burden in the world after cardiovascular disease and cancer, causing economic losses to society and patients’ families (1, 2). The disability rate of stroke is as high as 60%–80% (2), among which post-stroke hemiplegia is the main reason for the high disease burden (3). Currently, there is no particularly effective clinical treatment. Post-stroke hemiplegia may result in permanent disability if they do not receive timely and effective treatment (3, 4). The high cost of traditional rehabilitation, coupled with the cumbersome rehabilitation training methods, family commuting, poor treatment effects, and other factors make it difficult for patients to adhere to treatment or the treatment effects are few (5). In recent years, innovative rehabilitation strategies to improve motor function, represented by deep brain stimulation, have emerged (6–9). Deep brain stimulation can provide long-term chronic stimulation, and adjust the stimulation parameters during follow-up (10–12). Fine-tuning the treatment has achieved better therapeutic effects in many diseases that were difficult to treat in the past, such as Parkinson’s disease and depression (13, 14). Therefore, it has been used to improve motor function recovery after stroke and has been confirmed by human clinical studies. In a phase I clinical trial conducted by Baker et al. in 2023, 12 patients with moderate to severe upper limb motor deficits after unilateral stroke received cerebellar dentate nucleus-DBS treatment (7, 15). After treatment, the patient’s upper limb Fugl-Meyuer motor function scores improved by 7 points, the motor function of the upper limbs was significantly improved, and no serious complications occurred during the treatment (7).

The mesencephalic locomotor region (MLR) is critical for motor recovery (16–19). The MLR (Figure 1) is a phylogenetically conserved key motor control center in the brainstem, which is composed of two leading nuclei, namely the Pedunculopontine Nucleus (PPN) and the cuneate nucleus (CNF) (20–23). PPN is associated with exploratory behavior, and deep brain stimulation (DBS) of PPN in patients with Parkinson’s disease can reverse the freezing of gait (16, 23–28). CNF is the main control area for movement initiation, maintenance, and speed regulation, and research on stimulating this target with DBS to improve incomplete spinal cord injury (SCI) has aroused scientific and clinical interest (29, 30). Electrical stimulation of the rat MLR in an acute rodent stroke model to achieve near-physiological hindlimb movements during walking and swimming (20), and MLR-DBS improved walking speed and limb coordination (31). The MLR-DBS study confirmed that MLR-HFS does not affect the infarct area, however, it can regulate the area around the lesion and reduce neuroinflammation by affecting the cholinergic anti-inflammatory pathway (32–35). In particular, CNF high-frequency stimulation (HFS) can significantly reduce the neuroinflammation at the stimulation site. Inflammatory cytokines and chemokines, reduce the concentration of pro-inflammatory cells (23, 33). In addition, DBS can stimulate CnF glutamatergic neurons, activate their afferent or efferent fibers, and stimulate spinal reticular fibers to initiate movement within a short latency period (32, 33, 36–39). Judging from the above literature, MLR-DBS is a potentially effective treatment for post-stroke motor dysfunction, but the application of DBS in the treatment of post-stroke sequelae is still in the exploratory stage, and a large number of studies are still in the animal experiment and clinical verification stages (40). No large-sample clinical trials have been conducted. So we designed this multi-center randomized controlled clinical trial (RCT) (7). The leading purpose is to explore the safety and effectiveness of DBS in improving motor function in patients with post-stroke hemiplegia. The secondary purpose is to explore its potential therapeutic mechanism and provide clinical evidence support for the widespread application of DBS technology in post-stroke hemiplegia.

**Figure 1 fig1:**
[figure not shown]
Schematic illustration of the reticulospinal system. **(A)** Higher central nervous system centers of motion control send their signals to the mesencephalic locomotor region (MLR). The MLR is bilaterally linked to its downstream target, the gigantocellular reticular nucleus (NRG), which gives rise to the reticulospinal tract and drives the central pattern generators (CPG) for motoneuron activation and locomotion. **(B,C)** Horizontal section of the human **(B)** and cross section of the rat **(C)** midbrain at the level of the superior colliculi depicting the MLR (**B**: landmarks based on Afshar et al. 90; **C**: landmarks based on Paxinos and Watson 91). CNF, cuneiform nucleus; PPN, pedunculopontine nucleus. Based on https://www.neuroanatomy.ca/index.html.

## Methods and analysis

### Study design

The trial is a multicenter, prospective, double-blind crossover randomized controlled trial (RCT). The overall process is in Figure 2. In this study, we will include 62 moderate to severe post-stroke hemiplegia patients who had stable disease after 1 year of conservative treatment in multiple neuro medical centers in the General Hospital of the People’s Liberation Army of China et al. All patients included in the study will undergo deep brain electrode implantation. They will be randomly postoperatively divided into a DBS group and a control group, with 31 patients in each group. 1 month after surgery, the DBS group will be given electrical stimulation treatment, while the control group will undergo routine observation. Following up in the 3rd and 6th months after surgery. After the follow-up, all patients will stop electrical stimulation treatment for 2 weeks. After the 2-week washout period, the control group will start electrical stimulation treatment, and the DBS group will continue observation. Outpatient follow-up in the 6th and 9th months after surgery. After the follow-up, all patients will undergo electrical stimulation treatment. Observe for a long time. The leading outcome measure of follow-up is the pre-and post-change score on the Fugl-Meyer Assessment Upper Extremity Scale (FMA-UE). In addition, we will follow up on changes in the secondary outcomes of balance function, neuropsychiatric behavior, Post-stroke Spasticity, fall risk, activities of daily living, and quality of life.

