**Allocation**								
DBS group				×	×	×		
Control group							×	×

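### The protocol gives conflicting stimulation calendars, so month 12 may be a sham-controlled crossover visit or a visit with everyone stimulated, and month 6 is listed in both periods

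*Protocol article*

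**What the plan says.** Three places in the protocol article set out when stimulation is on.

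- **Study design.** The first period opens as follows: "1 month after surgery, the DBS group will be given electrical stimulation treatment, while the control group will undergo routine observation". It ends thus: "Following up in the 3rd and 6th months after surgery. After the follow-up, all patients will stop electrical stimulation treatment for 2 weeks". The crossover comes next: "After the 2-week washout period, the control group will start electrical stimulation treatment, and the DBS group will continue observation". The second period then closes with: "Outpatient follow-up in the 6th and 9th months after surgery. After the follow-up, all patients will undergo electrical stimulation treatment".
- **Table 2, Allocation rows.** The DBS group is marked at months 1, 3 and 6. The row labelled "Control group" is marked at months 9 and 12 only.
- **Abstract, Methods/design.** "Stimulation will be discontinued after 3 and 6 months, followed by a 2-week washout period". After the crossover: "Both groups will resume electrical stimulation at the 9th and 12th-month follow-ups". On the analysis it adds: "Post-12-month follow-up, motor-related scores will be collected for analysis, with the Fugl-Meyer Assessment Upper Extremity Scale (FMA-UE) as the primary metric".

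Under Outcome measurements and in Table 2, the primary scale is assessed at months 1, 3, 6, 9 and 12.

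**The concern.** In a crossover trial, each group's stimulation state at each visit defines the treatment comparison. Here that state depends on which section is read.

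The larger conflict is at month 12. Study design has everyone on after month 9, so month 12 offers no contrast between the groups. Table 2 has only the control group marked at month 12, which makes it a second-period visit with a contrast. The second conflict is at month 6, which Study design lists both as the visit before the washout and as a visit after it.

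If centres switch devices according to Study design and analysts assign treatment according to Table 2, stimulated patients in the DBS group are counted as sham at month 12. The expected difference at that visit is then zero by design, and including it pulls the estimate towards no effect. The Data analysis section does not settle the matter: it describes scores and changes from baseline at each visit and does not say which visits form the sham-controlled contrast.

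**Working it through.** The protocol states no figure for this point, so there is none to reproduce. The check is to write down each group's state at each visit under each statement and compare.

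**Stimulation state (DBS group / control group)**

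| Source | Month 3 | Month 6 | Month 9 | Month 12 |
|---|---|---|---|---|
| Study design, month 6 as end of period 1 | on/off | on/off | off/on | on/on |
| Study design, month 6 as a period-2 visit | on/off | off/on | off/on | on/on |
| Table 2 | on/off | on/off | off/on | off/on |
| Abstract, read literally | on/off | on/off | on/on | on/on |

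The abstract can also be read loosely, with both groups resuming only once those visits are done. It then matches Table 2.

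**Length of the periods**, taking the 2-week washout as half a month:

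- Period 1: 6 − 1 = 5 months.
- Period 2 under Study design: 9 − 6.5 = 2.5 months.
- Period 2 under Table 2: 12 − 6.5 = 5.5 months.

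**Illustration of the effect on the estimate.** Inputs: an effect of 7 points, taken from the Sample size section, and the assumption of no carryover and no period effect. The expected difference, DBS group minus control group, is 7 × (DBS state − control state), with on = 1 and off = 0.

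| Source | Month 6 | Month 9 | Month 12 |
|---|---|---|---|
| Study design, month 6 as end of period 1 | +7 | −7 | 0 |
| Study design, month 6 as a period-2 visit | −7 | −7 | 0 |
| Table 2 | +7 | −7 | −7 |
| Abstract, read literally | +7 | 0 | 0 |

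1. Period-2 effect with months 9 and 12 averaged equally: Table 2 gives (7 + 7)/2 = 7. Study design gives (7 + 0)/2 = 3.5. The literal abstract gives (0 + 0)/2 = 0.
2. Crossover estimate from months 6 and 12, as half of (month-6 difference − month-12 difference): Table 2 gives ½ × (7 − (−7)) = 7. Study design with month 6 ending period 1, and the literal abstract, both give ½ × (7 − 0) = 3.5.
3. Crossover estimate with an intact period 1 and months 9 and 12 averaged in period 2, under Study design: (7 + 3.5)/2 = 5.25, a loss of (7 − 5.25)/7 = 25%.

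The size of the dilution depends on how visits are combined. The zero difference at an all-on visit does not; it follows from the calendar under the stated assumptions.

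**The case against.** The strongest reply is that this is one slip. If the second pair of months in Study design was meant to be 9 and 12, that section agrees with Table 2 and with the list of assessment visits, and the loose reading of the abstract fits too. This is plausible, but the article does not say so, and the abstract's wording would still need correcting. Readers and centres should not have to guess.

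On month 6, the order of events in Study design puts the start of period 2 at about month 6.5, and both Table 2 and the abstract point to month 6 as the end of period 1. A period-2 visit at month 6 is therefore better seen as an impossible label than as a real alternative design. That is fair, and it makes month 6 the weaker half of the point. It is still an error in the text.

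Figure 2, said to show the overall process, is not available here and may show the intended calendar. It could not remove a contradiction between passages of text. Table 2 also does not define its mark as stimulation on, although the pattern fits the crossover.

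The objections to the numbers largely stand. The 7 points is a before-after improvement from the literature, not a difference from sham. The article nowhere says that months 9 and 12 will be pooled. The halving applies to period 2 alone; for the whole crossover estimate on the same premises the loss is 25%.

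Naming the analysis visits is often left to the analysis plan. When devices are switched on is not: that belongs in the protocol, and an analysis plan cannot choose between conflicting versions of it.

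**Conclusion.** The concern holds. At month 12 the DBS and control groups are on/on under Study design and under the literal abstract, and off/on under Table 2. Month 6 appears on both sides of the washout within Study design. Period 2 lasts 2.5 or 5.5 months depending on the source. The conflict must be fixed because it leaves open when devices are on and which primary-outcome visits carry a sham contrast.

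That conclusion rests on the text alone. The figures for dilution are illustrations: they assume a 7-point effect, no carryover, no period effect, equal weighting of visits, and centres following one section while analysts follow another. On those terms the period-2 effect falls from 7 to 3.5 points and the whole crossover estimate from 7 to 5.25.

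**What to change.** Reconcile the abstract, Study design and Table 2 into one calendar that gives, for each group, the stimulation state at every visit and the dates of the washout and of the switch to stimulation for all. Define the mark used in the Allocation rows of Table 2, and check Figure 2 against the result. Which calendar is intended is for the sponsor to state.

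Then add one statistical rule: only visits at which the groups differ in stimulation enter the randomised comparison, and visits with everyone on are reported separately as open-label follow-up. Because the Discussion says the trial is already running, the sponsor should also confirm which calendar the centres have followed.

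The document change costs some protocol wording and one corrected table. It needs no added patients or visits.

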**Figure 2 fig2:**
[figure not shown]
Brief flowchart of the entire study with draw. For patients whose electrode is not implanted in the ideal position in CT review after DBS implantation, the device can be temporarily left off, and the follow-up of clinical trials is excluded, and relevant conventional rehabilitation means can be actively given. The health status of patients can be observed at any time, and regular follow-up can be conducted. When all clinical trials are over, the effect of DBS treatment can be observed. If the effect of DBS treatment is better than that of the traditional control group, the electrode position should be adjusted again and DBS treatment should be performed again.

### Methods

#### Sample size

This study is a randomized, double-blind, active sham stimulation control design, and statistical experts determined that the sample ratio between the DBS group and the control group was 1:1. A review of the literature revealed that subjects’ upper limb FMA scores improved by an average of 7 points. Since this study was based on the changes in the mean FMA before and after DBS treatment, based on literature data, the mean FMA before DBS treatment was 21.92 ± 6.30, and the mean FMA after DBS treatment was 35.42 ± 12.23. This study is designed as a difference test to determine whether the mean of the DBS group (u1) is different from the mean of the control group (u2) (41, 42). The assumptions are as follows: H0: u1 − u2 = 0, H1: u1 − u2 ≠ 0. The two-sided significance level was 5%, the statistical power was 90%, and the dropout rate was 20% (43). The total sample size required for this study was calculated by PASS V.15 sample size calculation software to be 48 patients, with 24 people in each group. According to the possibility of electrode implantation deviation and other special circumstances leading to a lose, we included 62 patients, 31 in each group.

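### The sample-size paragraph does not say which difference and SD its 90% power and 48 patients refer to, and the 90% is not supported for the 7-point gain it cites

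*Protocol article*

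**What the plan says.** All the inputs stand in the Sample size section of the protocol article.

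- **First effect:** the literature showed that "subjects’ upper limb FMA scores improved by an average of 7 points".
- **Second effect and SDs:** "the mean FMA before DBS treatment was 21.92 ± 6.30, and the mean FMA after DBS treatment was 35.42 ± 12.23".
- **Test:** a two-sided comparison of the DBS group mean with the control group mean, allocation 1:1.
- **Settings:** "The two-sided significance level was 5%, the statistical power was 90%, and the dropout rate was 20" per cent.
- **Result:** the PASS calculation is reported in the words "software to be 48 patients, with 24 people in each group".
- **Further allowance:** enrolment is raised to 62 (31 per group) to cover electrode misplacement and other losses.

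The Study design section makes the primary outcome a pre-to-post change in FMA-UE. The Randomization section gives controls the same rehabilitation training, with weekly expert review, and stimulation set to zero. No SD of the change score, no pre-post correlation and no within-patient SD between periods is given.

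**The concern.** The paragraph prints two effects that differ by nearly a factor of two (7 and 35.42 − 21.92 = 13.5 points) and two SDs that also differ by nearly a factor of two. It names neither the difference nor the SD that was entered, so a reader cannot tell what effect the 90% power is for. The answer decides how a null result is read. If the calculation was for 13.5 points, a true difference of about 7 points could well be missed, while the stated 90% would invite the conclusion that DBS does not work. Every participant has bilateral electrodes implanted, so the trial's stated ability to answer its question should rest on a defined effect.

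**Working it through.** **Inputs (Sample size section):** difference d = 7 or 13.5; SDs 6.30 and 12.23; two-sided α = 0.05; power 0.90; dropout 20%; 1:1.

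**Formula.** The normal approximation per group is n = (1.960 + 1.282)² × (s₁² + s₂²) / d², with (1.960 + 1.282)² ≈ 10.51. The t-test value comes from the noncentral t distribution (Welch for unequal SDs). Dropout inflation is n / 0.80, rounded up.

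**Step 1: reproduce the 48, and try the other pairings.**

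| d | SDs | normal approx. | t-test n per group | after dropout | total |
|---|---|---|---|---|---|
| 13.5 | 12.23 / 12.23 | 17.2 | 19 | 24 | **48** |
| 7 | 6.30 / 6.30 | 17.0 | 19 | 24 | **48** |
| 13.5 | 6.30 / 12.23 | 10.9 | 13 | 17 | 34 |
| 7 | 6.30 / 12.23 | 40.6 | 42 | 53 | 106 |
| 7 | 12.23 / 12.23 | 64.1 | 66 | 83 | 166 |
| 13.5 | 6.30 / 6.30 | 4.6 | 6 | 8 | 16 |

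Two pairings give exactly 48 (19 / 0.8 = 23.75, so 24 per group). At 19 per group their power is 91.2% (13.5 points) and 91.5% (7 points).

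**Step 2: what each pairing assumes.**

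- *13.5 with 12.23.* The 13.5 is an uncontrolled before-after gain. Using it as u1 − u2 assumes that controls gain nothing, although they receive the same rehabilitation.
- *7 with 6.30.* This gives both groups the pre-treatment SD and drops the 12.23 printed beside it. Read as an SD of change, 6.30 would require √(6.30² + 12.23² − 2r × 6.30 × 12.23) = 6.30. That gives r = 12.23 / (2 × 6.30) = 0.97, a very high pre-post correlation.

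**Step 3: evaluable numbers.** If the extra enrolment is fully used, 31 per group becomes 24 (48/62). If the 20% dropout is then fully used, 24 × 0.8 = 19.2, so 19.

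**Step 4: power for 7 points, parallel groups, two-sided 5%.**

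| SD assumption | 19 per group | 24 | 31 |
|---|---|---|---|
| 12.23 in both | 40.4% | 49.3% | 60.2% |
| 6.30 / 12.23 | 57.1% | 67.8% | 79.2% |
| change score, r = 0.5 (SD 10.6) | 50.9% | 61.1% | 72.6% |
| change score, r = 0.8 (SD 8.1) | 73.4% | 83.2% | 91.6% |
| 6.30 in both | 91.5% | 96.5% | 99.0% |

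The correlations are assumptions; the protocol gives none. Over the wider range r = 0 to 0.9, the SD of change runs from 13.8 to 7.1, and power with 19 per group from 33% to 84%.

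**The case against.** Four points can be made for the sponsor.

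1. **The arithmetic reproduces.** This stands. A reader might infer from the conflicting figures that 48 patients at 90% power cannot be obtained from the printed inputs. It can, in two ways. The defect is that the text does not say which way was used, and that each way rests on an unargued assumption.

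2. **Power for 7 points may be adequate.** A reader might call the 90% simply false for 7 points. The document does not allow that: with SD 6.30 in both groups, 19 per group give 91.5%, and with all 31 evaluable and a correlation of 0.8, power is about 92%. What can be said is that the protocol states and defends neither condition.

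3. **40–57% is a pessimistic selection.** Partly right. It needs the raw post-treatment SD in one or both groups and both loss allowances used in full, whereas the extra enrolment covers a possible loss. The change-score range suits the stated endpoint better and is higher, though still below 90% for most of the combinations shown.

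4. **The trial is a crossover.** A within-patient analysis could have more power. As an illustration, assume SD 12.23 in both periods, 38 evaluable patients and no carryover: power for 7 points is about 68%, 83% and 93% at within-patient correlations of 0, 0.3 and 0.5. So 40–57% should not be read as what the crossover must deliver. But the Sample size section frames a two-group test, and the document gives no within-patient SD from which to claim the gain.

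**Conclusion.** The concern holds in this limited form. The paragraph cites two incompatible effects and two SDs and ties its 90% power and 48 patients to none of them. Of the two pairings that yield 48, one takes an uncontrolled gain as the treatment difference and the other ignores the post-treatment SD.

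The 90% is therefore unsupported for the cited 7-point gain. For a parallel-group comparison, power at 7 points is 40–57% with 19 evaluable per group and 60–79% with 31, when the post-treatment SD applies to one or both groups. It is 51–73% and 73–92% on the change-score scale at assumed correlations of 0.5–0.8. With 19 per group, 90% is reached in these calculations only if an SD of about 6.30 applies to both groups. The arithmetic is certain; which row describes the trial depends on an SD that the document does not give.

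**What to change.** Revise the Sample size paragraph to:

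- name the one between-group difference and the one SD of the analysed change score that were entered in the calculation;
- justify that difference net of the gain expected in controls who receive the same rehabilitation;
- restate the power for a 7-point difference, giving the SD or pre-post correlation assumed, the evaluable number per group, and whether the analysis is parallel-group or within-patient crossover (with its within-patient SD).

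The sponsor must say which pairing was used; the revised text should not guess it. The cost is a rewritten paragraph and probably a less favourable stated power. No extra patients and no change of design are needed.
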